### Analysis

The analysis will treat count outcomes as Poisson distributed. A number of multilevel factors can impact the outcomes, including site/clinics, city, time, and the type of the site (HTC vs. substance use rehab). Because individuals are clustered within sites and sites are clustered within a city, we need to consider the variance inflation factor that results in this clustering. We considered a number of approaches: using random effects, fixed effects, or Generalized Estimating Equations (GEE) considering population-averaged methods. Although a random effects model for sites seems a natural approach, we needed to consider fixed effects of the city and of the site type, which would leave little power left to estimate the random effects distribution. Consequently, we will also use two other methods, GEE and the fixed effects model, to assess sensitivity by comparing the results across these models.

We will use Stata Release 14 (College Station, TX) and SAS version 9.2 (Cary, NC). Data will be examined to determine the extent to which they meet appropriate distributional assumptions. We will use methods described by Ecob and Der to identify outliers in longitudinal models and use methods of case downweighting when extreme cases are identified [40]. Missing data will be handled using multiple imputation methods [41]. The patient-level analyses will be organized into three groups to examine (a) successful reduction of risk behaviors targeted by the WHC (i.e., effectiveness), (b) patient satisfaction, and (c) increasing the number of women receiving ART and adhering to ART, and being admitted to substance use rehab.

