To assess effectiveness, the analysis will compare changes from baseline to 6-month follow-up on the amount of alcohol consumption, biological and self-reported drug use, condom use at last sex, number of sex partners over the past 6 months, and values from scales that measure relationship power and communication. We will start with descriptive analyses, including measures of central tendency, and dispersion (e.g., means, medians, proportions, standard deviations). Bivariate analysis will include paired t-tests, Wilcoxon rank-sum, and tabular statistics and the chi-square test. For multivariable analysis, the xtlogit and xtgee function will be used to specify random effects or fixed effects, and will assume that the correlation matrix is exchangeable. The models will control for other covariates identified in bivariate analyses or hypothesized a priori (e.g., condom use is correlated with substance use). One of the most important covariates in the model will be measures of patient satisfaction. Model performance and fit will be assessed with incremental elimination of variables, likelihood ratio tests, and changes in the Akaike information criterion (AIC) and Bayesian information criterion (BIC) values.

Patient satisfaction analyses will be predominately descriptive to determine if satisfaction improves with each cycle, varies by type of clinic, and by participant characteristics (e.g., alcohol use, pregnancy status).

We assume that the prevalence of patients receiving or adhering to ART or receiving treatment for substance abuse are Poisson distributed and increase from baseline to follow-up. We will use a similar approach outlined in the effectiveness analysis for bivariate and multivariable analyses. Variables considered for multivariable analysis will include patient characteristics, measures of patient success with the WHC, patient satisfaction, and clinic-level characteristics (e.g., type of clinic, provider satisfaction).

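### The stated model-building rules use fit criteria undefined for the GEE fits, select covariates on the outcome data, and allow post-intervention variables into the effect models

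*Protocol article*

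**What the plan says.** All the statements are in the Analysis section of the protocol article, except where another place is named.

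- **Models.** For multivariable work, "the xtlogit and xtgee function will be used to specify random effects or fixed effects, and will assume that the correlation matrix is exchangeable". GEE has a declared role: "we will also use two other methods, GEE and the fixed effects model, to assess sensitivity by comparing the results across these models".
- **Covariate entry.** "The models will control for other covariates identified in bivariate analyses or hypothesized a priori (e.g., condom use is correlated with substance use").
- **Elimination and fit.** "Model performance and fit will be assessed with incremental elimination of variables", together with "likelihood ratio tests, and changes in the Akaike information criterion (AIC) and Bayesian information criterion (BIC) values". The sentence makes no distinction between xtlogit and xtgee.
- **Outcomes.** The effectiveness group covers "successful reduction of risk behaviors targeted by the WHC (i.e., effectiveness"). The outcomes listed include "amount of alcohol consumption, biological and self-reported drug use, condom use at last sex, number of sex partners over the past 6 months".
- **Patient satisfaction.** It is ranked among the covariates that matter most in the effectiveness model. Table 1 lists the satisfaction questionnaire (CSQ-8) for programme participants at the 6-month visit only.
- **ART and rehab models.** They follow a similar approach. Their candidate covariates include satisfaction and indicators of how well a woman succeeded in the programme.

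**The concern.** The effect of interest is a change from baseline to 6 months in the same women, with no parallel untreated group in the patient-level comparison. The coefficient for visit therefore carries the whole result, and any covariate that itself changes between visits can move it.

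The rules as written raise three questions. Can they be carried out for every named model? Do the reported P values and intervals mean what they appear to mean? Does the adjusted visit coefficient still estimate the programme's effect, or only what is left after part of that effect has been conditioned away?

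**Working it through.** The article gives no figure on this point, so there is none to reproduce. The check sets the statements against each other and against what each method provides.

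**1. Fit criteria and model type.** A likelihood ratio test compares maximised log-likelihoods, and AIC and BIC are penalised log-likelihoods.
- Random-effects xtlogit maximises a likelihood and fixed-effects xtlogit a conditional likelihood, so the criteria are available within each type of fit.
- xtgee with an exchangeable working correlation solves estimating equations and specifies no joint likelihood, so the three criteria are undefined. Some packages print an AIC after a GEE fit, but it comes from a working-independence quasi-likelihood, not from the exchangeable model fitted.
- The usual counterparts are Wald or score tests and QIC. The article names none of them.

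**2. Selection.** One entry route (bivariate analysis) and the elimination step both use the outcome data that later supply the estimate. Standard errors from the final model treat its covariates as fixed in advance, and no correction is stated. The a priori route avoids the screen, but the elimination step as described is not limited to screened variables.

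**3. Post-intervention covariates.** Take a linear model with two rows per woman. Let *c* be the visit coefficient without covariate M, *c′* the coefficient with M, *a* the mean change in M between visits, and *b* the coefficient of M in the adjusted model. Least squares gives

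c = c′ + a × b, so c′ = c − a × b.

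On the logit scale this is only approximate, because adding covariates also changes odds ratios for other reasons.

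| Covariate | Value of *a* | Consequence |
|---|---|---|
| Baseline value, repeated on both rows | 0 | c′ = c in the linear case |
| Current substance use, in a condom-use model | negative if the programme lowers use | with b negative, a × b is positive and c′ is below c |
| Satisfaction, repeated on both rows | 0 | no shift as a main effect, but only women with a 6-month score contribute unless it is imputed |
| Satisfaction interacted with visit | not applicable | visit coefficient becomes the change at a satisfaction score of zero |
| Satisfaction on the follow-up row only, zero at baseline | large | M nearly duplicates visit and competes with it |

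Satisfaction with a programme has no baseline value to enter, and success in the programme cannot exist before it. Substance use does have one: the section on patient-level data collection says the same measures are taken at both visits, so either value could be used. The article does not say which.

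The documents give neither *a* nor *b* for any of these covariates, so a × b cannot be computed.

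**The case against.** Several points on the other side stand.

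- **A crude effect survives.** Paired t-tests of change are planned, and the section on patient-level data collection describes effectiveness as a pre-post comparison. A reader might infer that the programme effect is lost altogether. It is not: an unadjusted change is reported beside any adjusted model.
- **The condom example has no timing.** It says only that two behaviours are correlated. A reader might infer that follow-up substance use will enter the condom-use model. The text permits this but does not state it. Satisfaction and programme success are firmer evidence, because they can only be post-intervention.
- **The sensitivity comparison is not void.** A reader might infer that covariate sets differing by outcome make the random-effects, fixed-effects and GEE results incomparable. That comparison is made within an outcome, and nothing says the set differs by model type.
- **The article is condensed.** Assigning a criterion to each fit is normal detail for an analysis plan. This softens the GEE point, but the sentence as written covers xtgee without exception.
- **Covariates may be chosen a priori, and elimination is described as a way to assess fit.** Both are true. The a priori route still has as its only example two behaviours the programme targets.
- **Selection among baseline covariates may matter little.** By the identity above, in a linear model with complete pairs they do not move the visit estimate. Selection matters more for covariates that change between visits and in logistic models.

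**Conclusion.** The concern holds as a fault in stated rules, not as missing detail. Likelihood-based criteria are attached to a set of models that includes GEE, for which they are undefined; the xtlogit fits are unaffected. Inference on the visit effect is not corrected for data-driven selection. Post-intervention variables are admitted to the effect models, explicitly for satisfaction and programme success, and possibly for co-targeted behaviours.

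Adjusting for follow-up values can bias the visit effect towards no change when the programme works partly through the adjusted behaviour. This conclusion assumes that the covariate enters at its current value and moves in the intended direction. No size can be given from the documents: any figure would depend on assumed effects, baseline levels of use and correlation between behaviours within a woman. The point should be corrected before analysis, but it does not invalidate the planned unadjusted comparisons.

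**What to change.** 1. For each patient outcome, estimate the visit effect with one pre-specified set of terms: design terms plus baseline characteristics such as age. Use the same set in the random-effects and GEE fits, with no bivariate screening or elimination.
2. Choose the design terms without redundancy. Each site pair enrols in a single cycle, so pair and cycle are one term. If all sites enter as fixed terms, site type is absorbed.
3. Do not enter the baseline outcome as a covariate where it is already a response row. State that time-invariant terms drop out of a fixed-effects xtlogit with the woman as panel, which then estimates the visit effect without them.
4. For xtgee use Wald tests, and QIC if models are compared. Keep likelihood ratio tests, AIC and BIC for likelihood-based fits, within one type of fit.
5. Move follow-up substance use, other co-targeted behaviours, patient satisfaction and programme-success measures to models labelled exploratory (mediation or correlates of change).

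The cost is a change of wording in the analysis section. No new data are needed, and there is less modelling work than under the present rules.

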### Setting

The WHC is being rolled-out sequentially in four HTC/healthcare clinics and four outpatient substance use rehab centers located in selected disadvantaged communities (townships) in Cape Town. These sites were identified and approved by the City of Cape Town Health Department. Each HTC/healthcare clinic was paired with a substance use rehab center based on geographic proximity, and each pair was randomized by computer into four succeeding 6-month implementation cycles where implementation of the WHC is taking place simultaneously at the paired sites.

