**Fig. 1 Fig1:**
[figure not shown]
Implementation science study design for the Women’s Health CoOp program

As depicted in Fig. 1, this study has 4 cycles spanning several years. Each implementation cycle of the WHC program lasts 6 months. Based on the findings from each cycle, we undertake a brief formative “lessons learned” evaluation. These periods between cycles inform backward- and forward-implementation strategies through mixed methods of brief staff surveys and focus group discussions (FGDs), allowing for modification of the WHC while preparing for training in the next cycle. Pre-, mid-, and end-of-implementation FGDs are conducted to inform the modifications, including training materials, curriculum, and implementation data collection. Pre-implementation FGDs involve setting the stage for entry into the clinics, so that barriers and challenges can be addressed. Mid-implementation FGDs explore initial results and help determine if additional modifications to the intervention are needed. End-of-implementation FGDs with clinic staff and patients explore satisfaction with the intervention and concerns with the program’s sustainability. This format provides back-and-forth feedback and dialogue with clinic staff on the implementation processes and outcomes for further refinement. Consequently, the clinics randomized to Cycle 1 will have the longest post-intervention observation period, with implementation sustainability measured through fidelity checks and quantitative surveys. Conversely, based on lessons learned throughout the earlier cycles, sites in Cycle 4 benefit from an intervention that is more refined and in the most scalable form.

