HIV testing is not part of the research because it is performed by clinic staff as part of standard clinic operations. As proof of HIV-positive status, participants must provide a clinic-issued document such as an antiretroviral (ARV) card or ARV medication with identifiable data linking to the participant, or they must consent the research staff to access their hospital records for their results. Viral load is also collected at baseline and 6-month follow-up from the South African National Health Laboratory Service (NHLS) database in the clinics. Viral load testing is also part of the standard of care and the clinics routinely perform HIV viral load testing 6 months after a patient begins taking ART and then 12 months later; however, these intervals may vary by clinic. Viral load test information will be used to validate self-reported ART adherence.

In each cycle, the objective is to enroll 120 women (60 from a HTC/healthcare clinic and 60 from a substance use rehab center) for a sample total of 480, and to follow each enrolled participant at 6 months, with an expected follow-up rate of 90%. At the end of the 6-month follow-up period, we will assess effectiveness of the program using pre-post comparisons to determine whether women reduced their AOD use, are adhering to their ARV regimen, have reduced their sex risk behaviors (e.g., using a condom at every sex act; less transactional sex), and have experienced less to GBV. At the end of each cycle, we will conduct FGDs with a subsample of women who participated in both workshops of the intervention and completed their 6-month follow-up appointment. These study activities will enhance our understanding of women’s satisfaction with the WHC program and suggest modifications to the program for broader acceptability and implementation that will be incorporated into the next cycle.

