### Power

We used the Stata command, *steppedwedge* [36], which is based on the equation developed by Hussey and Hughes [37] to calculate the detectable difference between participants’ adherence before and after their exposure to the intervention, given a sample size that is feasible and realistic in these clinic settings (*n* = 480; or 120 participants per cluster). We conducted two analyses based on the following parameters: 120 participants per cluster, 240 observations per cluster, and power of .80. The first analysis was used to calculate the detectable difference between participants’ self-reported percentage of ART adherence during the past month before and after the intervention. No previous research has estimated the percentage of ART adherence among South African women who use substances since the government approved the provision of ART to all people living with HIV, regardless of CD4 count. Consequently, we based our analyses on a national estimate of the average percentage of ART adherence in South Africa since the ART rollout (87%; SD = 17.28). Based on this estimate, we will be able to detect an increase or decrease in adherence of 4% or greater. Next, we calculated the detectable difference between the proportion of adherent (i.e., report 95% or greater adherence or are virally suppressed) participants before and after their exposure to the intervention. We based this calculation on previous research that has reported on the proportion of people who engage in substance use that are adherent to ART (56%) [38] and national estimates indicating that 55% of all people living with HIV are virally suppressed [39]. In regards to self-report adherence, we estimate that we will be able to detect a difference of 13% or greater. Similarly, we also estimate that we will be able to detect a difference of 13% or greater to examine the change in the proportion of women who are virally suppressed before and after the intervention.

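### Each cycle is one different clinic-rehab pair, so CSQ-8 scores by cycle cannot show whether satisfaction improves from cycle to cycle

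*Protocol article*

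**What the plan says.** The Setting section describes "four HTC/healthcare clinics and four outpatient substance use rehab centers". Neighboring sites form four pairs, one site of each kind in every pair. On allocation it says: "each pair was randomized by computer into four succeeding 6-month implementation cycles". Under Patient-level process and data collection, the target in each cycle is 120 women, 60 from one clinic and 60 from one rehab center, "for a sample total of 480". The Power section likewise works with "120 participants per cluster".

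Table 1 lists client satisfaction, measured by the CSQ-8, under acceptability. The source is WHC participants and the only time point is the 6-month follow-up.

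The Analysis section says that the satisfaction analyses will be mainly descriptive. Their purpose is "to determine if satisfaction improves with each cycle", and also to see whether satisfaction differs by clinic type and by participant characteristics. The same section names site and time among the factors that can affect outcomes. It does not say how a difference between cycles would be told apart from a difference between site pairs.

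**The concern.** An improvement across cycles is a statement about change over time. The data are four groups of women, each from a different community, each seen in a different calendar period, and each scored once. There is no earlier score from the same pair to set against a later one.

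If the Cycle 4 pair scores higher than the Cycle 1 pair, several explanations fit equally well: the program got better, that community or its staff differ, or circumstances changed over calendar time. A real gain could also be hidden by an unfavorable order of pairs. The text under Fig. 1 expects that "sites in Cycle 4 benefit from an intervention that is more refined and in the most scalable form", so a rising sequence of means would be easy to read as success of the refinement. At stake is the conclusion drawn from one secondary analysis.

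**Working it through.** The document gives no sample size, alpha or power for satisfaction by cycle, so there is no stated figure to reproduce.

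**1. One pair per cycle.** There are 4 pairs and 4 cycles, with 120 women per cycle and 480 in all. Since 4 × 120 = 480, and 480 / 120 per cluster = 4 clusters, no pair enrolls study women in a second cycle.

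**2. Pair or site as a fixed effect.** Take the 8 sites as rows of a design matrix.
- Intercept, pair and site type: rank 1 + 3 + 1 = 5. Adding cycle, as categories or as a linear score, leaves the rank at 5.
- Eight site indicators: rank 8. Adding cycle leaves it at 8.

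Cycle adds no information once pair or site is in the model, so its effect is not estimable. Site type is different: every cycle has one site of each type, so that contrast is not aliased with cycle.

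**3. Pair as a random effect.** The trend can then be estimated, from four pair means.
- Degrees of freedom: 4 − 2 = 2; two-sided 5% critical t = 4.30.
- Correlation of the four means with cycle number needed to reach it: t / √(t² + 2) = 4.303 / √(18.51 + 2) = 0.95.
- Permutation test over the 4! = 24 possible orders: smallest p-value 1/24 = 0.042 one-sided and 2/24 = 0.083 two-sided. A perfectly ordered result would not reach two-sided 5%.

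**4. What would happen if individual women were tested and pair ignored.** This test is not in the plan.
- Expected follow-up is 90%, so 0.90 × 120 = 108 women per cycle, assuming that all of them give a CSQ-8 score.
- The variance of the slope is inflated by about 1 + (108 − 1) × ICC, and the rejection rate under no trend is about 2 × [1 − Φ(1.96 / √inflation)].

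| Pair-level ICC (assumed) | Variance inflation | Rejection under no trend, nominal 5% |
|---|---|---|
| 0.01 | 2.07 | 17% |
| 0.02 | 3.14 | 27% |
| 0.05 | 6.35 | 44% |

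Simulation with 4 × 108 women gives 17.2%, 27.2% and 44.4%. A separate simulation gives 17.3% at 0.01, 44.4% at 0.05 and about 5% at an ICC of 0.

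**The case against.** **The analysis is mainly descriptive.** This stands in part. No trend test is stated, and the Analysis section says in general that clustering must be considered. A reader might infer from the 17% to 44% rates that the plan itself carries that error. It does not: the rates belong to an unplanned test, and they measure ignored clustering, which is a separate problem from aliasing. What remains is that the stated purpose is directional. Four means can be described; improvement cannot be determined from them.

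**Pairs were randomized to cycles.** This also stands in part. Randomization means that pair differences are not systematically related to cycle order, so the weakness is extreme imprecision and not a built-in bias. It also justifies treating pairs as random. It cannot separate cycle from pair in the single order that was realized, and it does nothing about calendar time, which runs with cycle.

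**The harm is inferred.** A reader might conclude that the plan will credit any rise to refinement of the program. The Analysis section names no cause, and the text under Fig. 1 describes what late sites receive; it is not an analysis claim. A reader might also take CSQ-8 to be the only quantitative participant-level check on refinement. The article gives it no such role: Table 1 places it under acceptability and lists other participant-reported measures at 6 months, on referrals and on services sought.

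**Within-pair contrasts could rescue the question.** They could not do so reliably. Mid-cycle modifications are conditional on what the focus groups show, and a before/after split within a cycle would also reflect calendar time and staff experience. The staff surveys compare the start and end of implementation. They measure neither patient satisfaction nor one version of the program against another.

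**Conclusion.** The point holds for the purpose stated in the Analysis section. Cycle and site pair coincide, so CSQ-8 by cycle cannot establish that satisfaction improves with each cycle. This rests only on the allocation and on the single 6-month measurement, both stated in the article, and it is true at any intraclass correlation. Under fixed pair effects the cycle effect is not estimable; under random pair effects it has 2 degrees of freedom and a two-sided permutation p-value of at least 0.083. The rates in the table rest on the assumed ICCs and on 108 scores per cycle, and apply only if women were tested as independent of pair.

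The reach is limited. The power calculation, the comparisons from baseline to 6 months and the comparison of satisfaction by clinic type are not touched. The change should still be made, because the plan as worded could turn a difference between four communities into a conclusion of improvement, and preventing this costs very little.

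**What to change.** Reword the satisfaction paragraph of the Analysis section:
- Report CSQ-8 descriptively by site pair, labeled with its cycle, and state that cycle, pair and calendar period coincide.
- Draw no conclusion that satisfaction improved across cycles, or that refinement of the program caused a difference.
- If a trend is tested at all, base it on the four pair means, with 2 degrees of freedom or by permutation, and state the 0.083 floor for the two-sided permutation p-value. Do not test it on individual women with pair ignored.
- Keep the comparison by clinic type.

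This needs no new data and no change in sample size. The cost is a weaker claim about satisfaction over the cycles.

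### Three yes/no outcomes (ART receipt, ART adherence, substance-abuse treatment) are assumed to be Poisson distributed; unless a robust or scaled variance is used, standard errors for adherence would be about 1.5 to 1.6 times too large

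*Protocol article*

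**What the plan says.** The Analysis section makes two separate Poisson statements. The first is for counts: "The analysis will treat count outcomes as Poisson distributed". The second is for outcomes that are not counts: "We assume that the prevalence of patients receiving or adhering to ART or receiving treatment for substance abuse are Poisson distributed". The second sentence also assumes that these prevalences rise from baseline to follow-up.

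For modelling the ART and treatment outcomes, the article then says: "We will use a similar approach outlined in the effectiveness analysis for bivariate and multivariable analyses". The effectiveness analysis it points to is described as follows: "the xtlogit and xtgee function will be used to specify random effects or fixed effects, and will assume that the correlation matrix is exchangeable". Model fit is to be judged by likelihood ratio tests, AIC and BIC. No variance estimator (model-based, scaled or robust) is named.

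The Power section treats adherence as a yes/no outcome, defined as women who "report 95% or greater adherence or are virally suppressed", and starts from 56% adherent and 55% virally suppressed. Its conclusion for the proportion is: "In regards to self-report adherence, we estimate that we will be able to detect a difference of 13% or greater". The same 13 points are given for viral suppression.

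**The concern.** A 0/1 outcome with prevalence p has variance p(1-p). A Poisson variable with the same mean has variance p, which is larger by the factor 1/(1-p). At 55-56% the variance is overstated more than twofold. This is under-dispersion relative to the assumed model, so the error makes intervals too wide and tests too reluctant to reject. It cannot create a false positive, but it can hide a real benefit.

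The text also pulls in two directions. The Power section works with a proportion, and the logit command is a binomial model. The sentence on prevalence assigns a different distribution to the same outcome. An analyst cannot follow all three.

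Adherence and viral suppression are the only patient outcomes with a power statement, so this is where a loss of sensitivity matters most.

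**Working it through.** **Inputs from the article.** Baseline 56% adherent and 55% suppressed; detectable difference 13 points; power 0.80; 4 clusters with 240 observations each (Power). 480 women and 90% follow-up, hence 0.9 x 480 = 432 (patient-level data collection). **Assumed here:** two-sided alpha 0.05, intracluster correlation (ICC) 0, five periods of 240/5 = 48 observations per cluster.

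**1. The plan's own figure.** With ICC 0 the Hussey and Hughes variance is I·s²/(I·U - W), where s² = p(1-p)/48, I = 4, U = 10 (treated cluster-periods) and W = 0+1+4+9+16 = 30.
- At 56%: s² = 0.2464/48 = 0.00513; variance = 4 x 0.00513/10 = 0.00205; SE = 0.0453; detectable difference = 2.80 x 0.0453 = 12.7 points. At 55% it is also 12.7. Stated: 13.
- Mean adherence (SD 17.28): s² = 298.6/48 = 6.22; SE = 1.577; 2.80 x 1.577 = 4.4. Stated: 4.

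The 13 points are thus reproduced with the binomial variance. This depends on ICC 0; with ICC 0.01 to 0.2 and total variance held fixed, the detectable difference is 14.6 to 15.6 points.

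**2. SE ratio at one prevalence.** Poisson/binomial = 1/sqrt(1-p): 1.49 at 55%, 1.51 at 56%.

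**3. SE ratio for the log prevalence ratio, independent visits.** Ratio = sqrt{(1/p1 + 1/p2) / [(1-p1)/p1 + (1-p2)/p2]}.
- 56% to 69%: 1.786 + 1.449 = 3.235; 0.786 + 0.449 = 1.235; sqrt(3.235/1.235) = 1.62.
- 55% to 68%: sqrt(3.289/1.289) = 1.60.

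**4. Rejection under no change at 56%.** 2[1 - Φ(1.96 x 1.51)] = 2[1 - Φ(2.96)] ≈ 0.003, against a nominal 0.05.

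**5. An analysis with exactly 80% power.** Φ(2.80 - 1.96 x 1.62) = Φ(-0.37) ≈ 0.36.

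**6. The paired baseline to 6-month comparison.** Site clustering is ignored. The power of a test using the Poisson SE is Φ[(δ - 1.96·SE_Poisson)/SE_true].
- 56% to 69%, δ = ln(0.69/0.56) = 0.209, no within-woman correlation. 432 women: SE_Poisson = sqrt(3.235/432) = 0.0865, SE_true = sqrt(1.235/432) = 0.0535, power 0.77 (binomial 0.97). 480 women: 0.0821 and 0.0507, power 0.83 (binomial 0.98).
- The same contrast simulated with exchangeable GEE, Poisson family, scale 1: about 0.95 (432 women, latent correlation 0.5) to 0.98 (480 women, latent correlation 0.6); robust SEs give above 0.99. The overall range is about 0.76 to 0.98.
- 56% to 64%, 480 women, δ = 0.134. No correlation: SE_Poisson = sqrt(3.348/480) = 0.0835, SE_true = sqrt(1.348/480) = 0.0530; power 0.28 against 0.71. Simulated with latent correlation 0.6: about 0.56 against 0.90.

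**7. High prevalence.** For an assumed 85% to 90%: 1/0.85 + 1/0.90 = 2.288; 2.288 - 2 = 0.288; sqrt(2.288/0.288) = 2.82.

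**The case against.** The strongest reply is that the article never commits to unscaled, model-based Poisson standard errors. It names a logit command, sends these outcomes to that approach, plans to compare random-effects, fixed-effects and GEE models, and says: "Data will be examined to determine the extent to which they meet appropriate distributional assumptions". Poisson regression of a binary outcome with robust variance is a recognised route to a prevalence ratio. A condensed article may leave the variance option to a fuller document. In a re-run of the 56% to 69% case, an estimated scale brought the SE to 0.99 of the robust SE, so the effect disappears.

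This stands, and it makes the size conditional. It does not remove the point. The Poisson sentence is a positive choice, not a detail left open. A 0/1 variable is known not to be Poisson before any data are seen, and no remedy is attached to the planned check. Likelihood ratio tests, AIC and BIC rest on the assumed likelihood, and a robust SE does not repair them.

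It is also fair that the error is conservative, and that the 36% applies to an analysis sitting exactly at 80% power, not to the paired comparison of all women.

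**Conclusion.** The Poisson assumption is wrong for these three outcomes and conflicts with the proportion-based sizing and the logit command. If it is carried into unscaled, model-based standard errors, they are about 1.5 to 1.6 times too large for adherence at 55-56% rising by 13 points. The main harm is to real changes smaller than 13 points. With xtlogit, robust variance or an estimated scale, the inflation does not arise.

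Four stronger readings might be inferred, and the article does not support them:
- *The 80% power is lost.* In the paired analysis at 13 points, power stays at about 0.76 to 0.98 even with the Poisson SE. The article states no power for ART receipt or substance-abuse treatment, so none can be lost there.
- *Standard errors are up to 2.8 times too large.* That needs a prevalence near 85-90%, which is an assumption. The 87% in the Power section is a mean adherence percentage, not a proportion of women. The only ART-receipt rate given, 16% in the Pretoria background research, would imply 1/sqrt(0.84) = 1.09.
- *Every sized outcome is affected.* The statement "we will be able to detect an increase or decrease in adherence of 4% or greater" concerns a continuous mean and is untouched.
- *A one-sided test is planned.* Assuming that prevalences increase may only express a hypothesis; no one-sided test is stated.

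**What to change.** In the Analysis section, replace the Poisson sentence for ART receipt, ART adherence and substance-abuse treatment with a binomial model for the paired 0/1 data: for example xtgee with binomial family, woman as the panel, visit as predictor and robust standard errors, reporting the change in prevalence. If a prevalence ratio is wanted, use a log-link model with robust standard errors. State a two-sided test, which matches the two-directional wording in the Power section. Keep Poisson or another count model for true counts, such as number of sex partners. The cost is one sentence and a change of model family; no new data and no change in sample size are needed.
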